### Intervention description {11a}

The Soterix tDCS kit [19] will deliver 20-min stimulation sessions using two 5×5 cm sponge electrodes. The stimulation montage will comprise left DLPFC anodal or sham stimulation. The anodal electrode will be placed over the area corresponding to the left DLPFC (F5 of the EEG10–20 international system) and the reference (cathodal) electrode over the right supraorbital ridge. The active stimulation condition will use a constant current of 2mA, delivered via current ramps over 10 s at the onset and offset of stimulation, respectively. For sham stimulation, the current will be delivered only in the first 10 s, after which the stimulation will cease but with the electrodes still in place throughout the session.

The intervention will be delivered in a private room at Providence Care Hospital in Kingston Ontario or at the residential home where the participant is residing if they are unable to travel. The intervention will be delivered by a research assistant under the supervision of the principal investigator.

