### Provisions for post-trial care {30}

Patients will be informed what arm (treatment or sham) they were allocated to at the end of the study. They will also be advised to contact the study's principal investigator should they experience any adverse effects following each session. Additionally, participants will continue to receive usual care at the discretion of the treating psychiatrist or care team. It usually involves a combination of behavioural approaches, psychosocial interventions, and psychotropic medications.

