**Fig. 1 Fig1:**
[figure not shown]
Trial CONSORT diagram. Stop signal task (SST), Behavior Problems Inventory (BPI), Barratt Impulsiveness Scale version 11 (BIS-11), Modified Overt Aggression Scale (MOAS)

Participant healthcare records will be examined to obtain information concerning the diagnosis of IDD, demographics, number and duration of admissions to psychiatric institutions, and current psychotropic medication regime. A member of staff at the participant’s residence with good professional knowledge of the participant will be asked to complete the BPI and MOAS at baseline and 1 week after the last tDCS stimulation. At baseline, participants will be asked to complete the modified BIS-11, and SST. Three tDCS sessions will be delivered over three successive days (one session daily). Participants will be asked to repeat SST at the end of the third session (Fig. 1). Additionally, a tDCS adverse effects questionnaire will be administered following each tDCS treatment to detect adverse effects. At 1 week and also 1 month following the third and final treatment, participants will complete the BPI and MOAS and will be debriefed to unblind them to treatment arm.

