### Recruitment {15}

Participants will be recruited over 24 months from clinics, inpatient units, and community residential homes for people with IDD.

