## Assignment of interventions: blinding

### Who will be blinded {17a}

This a single-blinded study where participants will be blinded to treatment allocation. Professionals who complete MOAS and BPI-S will also be blinded to treatment allocation. To minimise bias, the principal investigator and research assistant will be initially blinded to the allocation sequence. This will be generated by a Queen’s University independent faculty member who is not involved in the study, and then communicated to the research assistant administering the intervention after the completion of baseline measures. It is anticipated that having the research assistant unblinded is unlikely to introduce assessment bias since all the study questionnaires will be completed by the participants and professionals involved in their care, who will be blinded to the treatment allocation. Participants will only be unblinded to the treatment allocation if they developed a serious adverse reaction such as self-harm or serious violence. To assess the robustness of blinding, participants will be asked to guess their treatment allocation after the last tDCS session.

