### Adverse event reporting and harms {22}

tDCS is considered to be a safe technique, but some small risks are recognised. A review of 567 tDCS sessions and from questionnaire responses from 102 participants [33] reported that the most common side-effect (reported by 70% of participants) is that of a tingling sensation under the electrodes. This is present during and shortly after the period of stimulation and has no adverse effects or risks. Fatigue or tiredness during the stimulation is the next common report (by about 35% of participants), and this may continue for a short period afterwards. This may occur when prolonged and uninteresting tasks are used during the experiment. Headaches after stimulation may occur in less than 10% of the participants. Headaches are usually mild and can be treated with normal over-the-counter painkillers, if required. There is no evidence that tDCS leads to any change in frequency or severity of headaches. Overall, less than 20% of the participants rated the stimulation procedure as mildly unpleasant and 80% reported that it was not unpleasant. In theory, tDCS might induce seizures, but this has never been reported in the scientific literature.

Potential risks will be completely disclosed to the participants as well as what to do should participants experience any side effects. For instance, should the tingling sensation become painful, the treatment will be stopped. The psychological or emotional risk is minimal; this risk will be mitigated with education and assurance from the study team. Additionally, participants will be debriefed at the end of each session and advised to contact the principal investigator if they experienced any adverse effects as a result of participation in the study. If a serious adverse event occurs during the treatment sessions, local staff (clinic, hospital, institutional) will be immediately notified and emergency protocols followed. We are not anticipating any adverse events serious or otherwise. However, should one occur, it will be documented and reported to the Research Ethics Board.

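### The protocol gives three conflicting times for telling participants their arm; if the follow-up debrief is applied, disclosure runs alongside recruitment and may weaken the blind of later MOAS and BPI-S ratings

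*Protocol article*

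**What the plan says.** Three sections of the protocol article say when a participant learns the allocation.

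- **Participant timeline {13}**, in the text after Figure 1, for the 1-week and 1-month contacts: "participants will complete the BPI and MOAS and will be debriefed to unblind them to treatment arm". The sentence ties the debrief to each participant's own follow-up and does not say which of the two contacts is meant.
- **Provisions for post-trial care {30}**: "Patients will be informed what arm (treatment or sham) they were allocated to at the end of the study". This could be the end of that participant's involvement or the end of the trial.
- **Who will be blinded {17a}**: "Participants will only be unblinded to the treatment allocation if they developed a serious adverse reaction such as self-harm or serious violence".

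The blinding section also says of the raters: "Professionals who complete MOAS and BPI-S will also be blinded to treatment allocation". It argues that an unblinded research assistant is unlikely to cause assessment bias, because the questionnaires are completed by blinded participants and blinded professionals. Under the timeline and Outcomes {12}, MOAS and BPI-S are informant-rated, and the informant is a staff member at the participant's residence.

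On recruitment: "Participants will be recruited over 24 months from clinics, inpatient units, and community residential homes for people with IDD". Sample size {14} acknowledges clustering by inpatient unit or care home, but expects most participants to come from the community.

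**The concern.** The primary outcome is a subjective rating by someone who knows the participant well, so its credibility rests on the rater not knowing the arm. A debrief at each participant's own follow-up releases allocations one at a time, while others are still being enrolled, treated and rated.

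This differs from the more direct problem that a debrief at the 1-week contact would come before the same participant's day-38 rating. Moving the debrief to after each participant's own day-38 rating would cure that problem and leave this one.

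If a home, unit or rater contributes more than one participant, staff or a later participant may know how an earlier case was allocated. Any expectation formed that way could colour later MOAS and BPI-S ratings, and a positive result would be open to that explanation.

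**Working it through.** **1. The three statements side by side.** The timeline gives routine disclosure at 1 week and/or 1 month. Post-trial care gives routine disclosure at an undefined end. The blinding section gives no routine disclosure at all. Taken literally, they cannot all be followed. Only the first, or the second read as the participant's own end, produces rolling disclosure.

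**2. Overlap with recruitment if the timeline is followed.** Inputs: 60 participants (Sample size {14}); 24 months (Recruitment {15}); ratings at day 10 and day 38 (Outcomes {12}). Even accrual is an assumption.

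- Rate: 60 / 24 = 2.5 per month.
- Debrief at day 38: 38 / 30.44 = 1.25 months; enrolled by then 2.5 × 1.25 = 3.1; still to enrol 60 − 3.1 = 56.9, about 57 of 60 (95%).
- Debrief at day 10: 10 / 30.44 = 0.33 months; enrolled by then 0.8; still to enrol about 59 of 60.

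These figures count people enrolled after the first disclosure anywhere in the trial. They show that disclosure and recruitment overlap almost completely. They do not show how many people are exposed to someone else's disclosure.

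**3. Can one allocation inform another?** One person's arm does not by itself reveal the next person's. Two indirect routes are possible.

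- *Learned cues.* The active arm receives 2 mA for a 20-minute session; for the other arm, "For sham stimulation, the current will be delivered only in the first 10 s". Of tingling, the harms section says: "This is present during and shortly after the period of stimulation". A disclosed case attaches an arm to a reported experience.
- *Block randomisation* (Sequence generation {16a}; no block size is given, so 2, 4 and 6 are assumed). Suppose someone knows every earlier allocation in the block and always guesses the arm with more places left. For a block of 2, the chance of a correct guess is (1/2 + 1) / 2 = 75%. For a block of 4, the four positions give 1/2, 2/3, 2/3 and 1, which average 71%. Enumerating blocks of 6 gives 68%. Chance is 50%. The next allocation is certain for 50%, 33% and 25% of assignments respectively. These are upper bounds: they require block members to share the same informed staff and each debrief to precede the next rating.

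**4. Who could be exposed?** Recruitment from inpatient units and community residential homes, and treatment at the residence for those unable to travel (Intervention description {11a}), make shared settings possible. The protocol gives no number sharing a home, unit or rater. Without it, no bias can be computed.

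**The case against.** The strongest reply is that rolling disclosure is not the settled plan. The blinding section's rule excludes it, and so does the post-trial section if it means the end of the trial. The blinding rule can also be read as covering only the period of participation, which would make it compatible with disclosure at trial end. This stands in part: what is established is a conflict, and the leakage risk is conditional on how the conflict is resolved. Neither section overrides the timeline, however, and the timeline is the text that site staff would work from.

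A reader might go further and infer that care staff will learn allocations, so that later ratings are no longer blind. The documents do not support that. The debrief is addressed to the participant, not the rater. No section says that participants share homes or raters, and Sample size {14} expects mostly community recruits. Community recruitment can still include staffed shared homes, so the possibility remains.

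The cue route is also weaker than it looks. The 70% tingling figure comes from a general review of tDCS sessions, not an active-versus-sham comparison. The information letter describes tingling at switch-on and just after, and sham also delivers current at onset. Explanation for the choice of comparators {6b} says that 10 s is enough to preserve blinding and that this sham has been validated. Sessions take place in a private room at the hospital, or at the residence. Those statements do not address someone who already knows a labelled case, but they make the route a possibility only.

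Nor can a bias be obtained by multiplying assumed shares. Taking 25% to 50% of participants exposed, 25% to 50% of those inferring the arm, and a shift of 0.3 to 0.5 SD gives 0.25 × 0.25 × 0.3 = 0.02 SD up to 0.5 × 0.5 × 0.5 = 0.125 SD. None of the three inputs is in the documents. The benchmark is unclear too: Sample size {14} labels its 0.30 as d, but uses it in a repeated-measures ANOVA calculation, where it would normally be f (d = 0.6 for two groups).

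Finally, prompt debriefing has value for participants with IDD. That is a real cost of waiting.

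**Conclusion.** The point holds in conditional form. The protocol states three incompatible times for telling participants their arm, and that needs correcting whatever its consequences. If the timeline is followed, disclosure overlaps nearly all of recruitment: about 57 of 60 participants would enrol after the first day-38 debrief, assuming even accrual. Where participants share a home, unit or rater, this may weaken the blinding of MOAS and BPI-S ratings that the protocol uses to argue against assessment bias. The 95% should not be read as the share of participants rated unblinded. The size of the bias, and whether any arises, cannot be estimated from the documents. The correction should be made because it is cheap and protects a subjective primary outcome.

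**What to change.** - **Participant timeline {13}:** remove the unblinding debrief from the 1-week and 1-month contacts.
- **Provisions for post-trial care {30}:** define the end of the study as after the last participant's day-38 MOAS and BPI-S have been rated and the data locked.
- **Who will be blinded {17a}:** align the sentence restricting unblinding with that definition, leaving the emergency unblinding provisions, including {17b}, as they stand.
- **Disclosures already made:** these are possible, since recruitment began on 1 July 2021 and this protocol version is dated 7 January 2022. Log the date and residence for each, and run a sensitivity analysis of MOAS excluding participants rated later from the same home or unit. With at most 60 participants, this would be supportive rather than conclusive.

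The cost is a short amendment, a simple log and one extra analysis, with no new outcome data. The drawback is that the earliest participants wait up to about two years to learn their arm.

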### Sample size {14}

A power calculation conducted using repeated measures ANOVA (G*Power) yielded a total sample size of 50 participants (effect size=0.30, power=95%, *α* = 0.05). To allow for an attrition rate of 20%, we will aim to recruit 60 participants (30 per arm). These parameters were based on other studies involving the use of tDCS to modulate cognitive and behavioural functioning [30, 31]. Indeed, Minarik and colleagues [30] recommended small to intermediate effect sizes (between *d*=0.4 and *d*=0.5) for tDCS studies. We opted for an effect size of *d*=0.3 to improve precision. Furthermore, sample size calculation by Cosmo and colleagues [31] yielded 25 participants per arm for a power of 80% and bidirectional type I error probability of 0.05%. To allow for an attrition rate of 20%, a final sample size of 60 was considered sufficient by Cosmo and colleagues to detect a 50% difference in performance on the inhibitory control task in the active tDCS group, and a 10% difference in the sham tDCS group. While we acknowledge the importance of accounting for clustering by in-patient/care home, given our clinical experience, we anticipate that most of the participants will be recruited from the community. Furthermore, given the special nature of the population in this study and the funding constraints, it would be unrealistic to aim to recruit larger numbers. Nevertheless, we believe that the sample size of 30 participants per study arm is sufficiently large to detect differences between the effects of active and sham tDCS.

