## Statistical methods

### Statistical methods for primary and secondary outcomes {20a}

Behavioural outcome measures will be analysed using the Statistical Package for Social Sciences (SPSS; Version 26). A 2 × 2 Repeated Measures ANOVA will be performed with group allocation (active tDCS vs. sham tDCS) and time (pre- vs. post-tDCS stimulation). Post tDCS measures for MOAS, SST, and BPI-S will be treated separately as repeated measures. Total scores on BIS-11 will be entered into the analysis as a covariate. Significant main effects and interactions will be explored using simple effects analysis. For instance, within-subject factors will be used to compare changes in outcome variables between the groups over time. A greater reduction in the total scores on MOAS in the active tDCS group than the sham tDCS group would be considered a successful primary outcome. Greater reductions in the total scores on BPI and greater increases in Stop Signal Reaction Time in the active tDCS group than the sham tDCS group would be considered successful secondary outcome. A *p* value of < 0.05 will be considered as statistically significant for the primary outcome measure. For secondary outcomes, multiple comparisons will be controlled for with Bonferroni correction and a *p* value of less than 0.0125 will be considered statistically significant.

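### The sample-size section claims 95% power with 50 participants for an effect it calls d=0.3; under plausible correlations those figures do not fit together, and 60 recruits less 20% leave 48, not 50.

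*Protocol article*

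**What the plan says.** All the figures stand in one paragraph of the protocol article, Sample size {14}.

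- The calculation, a repeated-measures ANOVA run in G*Power, is reported to have "yielded a total sample size of 50 participants (effect size=0.30, power=95" per cent), with alpha 0.05. The metric of the 0.30 is not named at that point. Nor are the correlation between measurements, the number of measurements, or which of the ANOVA tests was powered.
- The description of the effect: a cited methods paper "recommended small to intermediate effect sizes (between *d*=0.4 and *d*=0.5) for tDCS studies", and then "We opted for an effect size of *d*=0.3 to improve precision".
- The recruitment target: "To allow for an attrition rate of 20%, we will aim to recruit 60 participants (30 per arm").
- Further support: a second cited study needed 25 per arm for 80% power and settled on 60 participants, its target being "a 50% difference in performance on the inhibitory control task in the active tDCS group, and a 10% difference in the sham tDCS group".
- The conclusion: 30 per arm is judged large enough to detect a difference between active and sham stimulation.

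Statistical methods {20a} fixes the test to which this applies. It is a 2 × 2 repeated measures ANOVA (arm by pre/post), with success defined as a larger fall in total MOAS score in the active arm. That is the group-by-time interaction. On the level of significance: "A *p* value of < 0.05 will be considered as statistically significant for the primary outcome measure".

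**The concern.** Read together, these sentences claim 95% power, with 25 participants per arm, for a standardised difference of 0.3, and present that difference as more cautious than the usual 0.4 to 0.5. An effect that small normally needs hundreds of participants for 95% power. G*Power's repeated-measures ANOVA routine takes Cohen's f as its effect size, so a 0.30 that appears first as the input to that routine and then as d raises the question whether one metric was taken for the other.

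What is at stake is how the result is read. If the claim stands, a non-significant MOAS comparison can be presented as coming from a trial well powered for a small effect. The recruitment target also rests on an allowance for loss that should leave the required number evaluable.

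**Working it through.** **Inputs from the protocol.** Total N=50, 1:1 allocation, effect size 0.30, power 95%, alpha 0.05, 20% attrition, 60 recruited; 2 × 2 design with the interaction as the test of interest. **Assumed, because not stated:** the correlation r between measurements (varied), and m=2 measurements (m=3 also shown, since MOAS is taken at baseline, day 10 and day 38).

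**Formula.** For the within-between interaction, the noncentrality is λ = N f² m/(1−r), referred to a noncentral F with (m−1) and (N−2)(m−1) degrees of freedom.

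**1. Reproducing the plan's figure, with 0.30 read as f.**
- m=2, r=0.5: N=40 is enough for 95%. At N=50, λ = 50 × 0.09 × 2/0.5 = 18.0 and power is 98.6%.
- m=2, r=0.35: λ = 50 × 0.09 × 2/0.65 = 13.85 and power is 95.4%. So N of about 50 appears at r of about 0.34 to 0.35.
- m=3: N=50 appears at r of about 0.16 to 0.18.

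The figure of 50 can therefore be obtained from f=0.30, but only with a correlation that the protocol does not give.

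**2. What f=0.30 means.** In a balanced 2 × 2 interaction, a between-arm difference in change of δ (single-time SD units) gives cell effects of ±δ/4, so f = δ/4. Then f=0.30 is δ = 4 × 0.30 = 1.2 SD.

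**3. The stated effect, with 0.30 read as d.** With δ = d = 0.3, f = 0.3/4 = 0.075 and λ = N d²/(8(1−r)). At N=50 and r=0.5, λ = 50 × 0.09/4 = 1.125.

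| r | λ | Power at N=50 |
|---|---|---|
| 0 | 0.56 | 11% |
| 0.3 | 0.80 | 14% |
| 0.5 | 1.13 | 18% |
| 0.7 | 1.87 | 27% |
| 0.8 | 2.81 | 38% |
| 0.9 | 5.63 | 64% |

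Power of 95% needs r of about 0.96. The total N for 95% power is 580 at r=0.5 and 350 at r=0.7. With all 60 retained and r=0.5, power is 21%. Even d=0.5, the top of the cited range, has 41% power at N=50 and r=0.5.

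**4. A looser conversion.** Some users convert d=0.3 to f = d/2 = 0.15. In this interaction that is a 0.6 SD difference in change (4 × 0.15), not 0.3. Power at N=50 is then:
- two measurements: 55% (r=0.5), 77% (r=0.7);
- three measurements: 62% (r=0.5), 85% (r=0.7).

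It reaches 95% at r of about 0.83 (two measurements) or 0.79 (three).

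**5. Attrition.** 50/(1−0.20) = 62.5, so 63 are needed, or 64 for equal arms. 60 × 0.80 = 48. The target of 60 equals 50 × 1.2, and it covers a loss of 10/60 = 16.7%.

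**6. What 48 evaluable participants can detect** (2 × 2 interaction, two-sided alpha 0.05):

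| r | 80% power | 95% power |
|---|---|---|
| 0.5 | 0.83 SD | 1.06 SD |
| 0.7 | 0.64 SD | 0.82 SD |

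**The case against.** The strongest reply is that the protocol gives no correlation, so no single power figure can be set against the 95%. That is right. A reader might infer that the trial's true power is 18%, but that value belongs to r=0.5 and to d defined as a difference in change in single-time SD units. What the documents support is a range, and 95% lies outside it for every r up to 0.9.

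A reader might also infer that 50 participants can be reached only with f=0.30. That is not so: f=0.15 also gives 95% power at N=50 if r is about 0.83 (two measurements) or 0.79 (three). These correlations are high but not impossible. They do not rescue the text as written, because none is stated and because f=0.15 in this interaction is a 0.6 SD difference in change, twice the effect named.

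That f was entered and later called d is likewise an inference. It is well supported: the routine takes f, f=0.30 can yield about 50, and the same number is then set beside d=0.4 to 0.5. The protocol does not document it, and the finding does not depend on it.

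It is tempting to argue that the second cited study assumes a very large effect, by treating its 50% and 10% as responder proportions. The protocol does not say that they are proportions; they may be percentage changes in a task score. No standardised effect can be drawn from them. What can be said is that the calculation is described as having 80% power on an inhibitory control task, so it does not by itself support 95% power for d=0.3 on MOAS.

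On attrition, the shortfall is two participants. At f=0.30 and r=0.35, power moves only from 95.4% (N=50) to 94.6% (N=48). The planned intention-to-treat analysis with carry-forward or multiple imputation keeps dropouts in the dataset, though it does not restore the lost information. This part is minor.

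The section also says that larger numbers would be unrealistic for this population and budget. That is a fair reason for the target, but not for the power attached to it.

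**Conclusion.** The concern holds as an incompatibility between stated figures. An effect of d=0.3, a total of 50 participants and 95% power do not go together under plausible assumptions. For the planned 2 × 2 interaction at two-sided alpha 0.05, power is 11% to 38% over r from 0 to 0.8, and 95% would need r of about 0.96. The more generous f=0.15 reading still falls short at moderate correlations (55% to 77% with two measurements and 62% to 85% with three, for r of 0.5 to 0.7).

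If the input was f=0.30, the calculation was for a 1.2 SD difference in change. That is four times the effect described, so the claim to be more cautious than d=0.4 to 0.5 would be reversed. The size of the discrepancy rests on the assumed correlation and on the definition of d; its existence does not, short of very high correlations.

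The attrition allowance is a separate, smaller and purely arithmetical error: 48 evaluable, not 50.

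The power claim should be corrected before the results are interpreted, because it concerns the primary outcome and can be put right in the text alone.

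**What to change.** Keep the recruitment target of 60 and restate the section:

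- Name the effect metric actually entered in G*Power, with the assumed correlation, the number of measurements and the test (interaction or between-arm).
- Remove or correct the sentence that calls the effect d=0.3 and more precise, and withdraw the 95% power claim for it.
- Replace the conclusion that 30 per arm is large enough with the difference that 48 evaluable participants can detect: about 0.83 SD at 80% power and 1.06 SD at 95% for r=0.5; 0.64 SD and 0.82 SD for r=0.7. Say that the correlation is assumed.
- Give the evaluable number as 48, or the attrition allowance as 16.7%.

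The cost is rewording and a less favourable power statement. No additional participants are needed.
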